#### Secondary clinical outcome measures

Additional patient clinical outcome data were obtained from the electronic medical records at the MNCLHD and NBMLHD sites throughout the pre-intervention and implementation periods. The collected data included:

Body mass index (BMI) and BMI standard deviation.Method of insulin administration (fixed insulin dose regimes, flexible multiple daily injections, insulin pump therapy).CGM metrics: Sensor wear time, time in range (3.9 mmol/L–10.0 mmol/L, 70 mg/dL–180 mg/dL), time in tight range (3.9 mmol/L–7.8 mmol/L), time below range (<3.9 mmol/L, <70 mg/dL), time in hypoglycemia, level 2 (<3.0 mmol/L, <54 mg/dL), time above range (>10 mmol/L, >180 mg/dL), and time in hyperglycemia, level 2 (>13.9 mmol/L, >250 mg/dL).Adherence to international recommendations for diabetes-related complication screening (30) in the 12 months preceding implementation to study completion.Number of hospitalizations for diabetes in the 12 months preceding implementation to study completion (not including initial diagnosis).

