**Methods:**

A pre–post-implementation study will be conducted in three hospitals: two non-metropolitan sites in the Mid-North Coast Local Health District (MNCLHD) and one metropolitan site in the Nepean Blue Mountains Local Health District (NBMLHD). An education program will be delivered to clinicians with written resources and clinical support. All children and young people aged 0–18 years with T1D receiving care at these sites receive SWIIM for diabetes management. Data will be collected over an 18-month implementation period with retrospective pre-intervention data for comparison. The primary outcome was the change in HbA1c levels over the implementation period. Secondary outcomes included continuous glucose monitoring (CGM) metrics, insulin therapy modality, adherence to complication screening, hospitalization rates, and program feasibility indicators. Acceptability will be assessed using validated patient- and clinician-reported measures. A cost-effectiveness analysis will be performed to determine the financial impact of implementing the SWIIM over standard care.

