
The model of care will be delivered to families with the following components:

Inpatient insulin initiation and education program for newly diagnosed type 1 diabetes: A standardized education package for newly diagnosed type 1 diabetes was delivered by diabetes nurse educators, dietitians, and social workers over a 5–7-day inpatient admission. Medical officers initiate and adjust subcutaneous insulin doses. Receipt of education is verified by an education checklist completed by families and educators and a carbohydrate counting quiz performed prior to discharge. Following discharge, daily phone follow-ups for ongoing education and insulin dose adjustment were provided for 7–10 days.Three monthly outpatient follow-ups: Young people will be reviewed by a diabetes educator and dietitian 2 weeks after diagnosis. Thereafter, young people are reviewed in outpatient clinics four times per year by physicians. At least one review each with the diabetes educator, dietitian, and social worker (where available) is arranged annually. During outpatient appointments, insulin doses are titrated, and SWIIM management principles are communicated to patients and families.School education: Schools, preschools, and daycare centers that each patient attended received educational session delivered by a diabetes educator. An individualized school plan was provided for each patient. Schools can contact diabetes educators by phone during business hours. The school visit is repeated if there is a change in therapy or the child attends a new school.Written resources: A printed 10 Essential Habits document summarizing key SWIIM principles will be provided to all families from the initial inpatient admission or at the first outpatient clinic review during implementation. Additional printed resources will be provided to the local teams and distributed by clinicians at their discretion, including written and pictorial dietary guidance, insulin dosing guidance, and exercise management strategies. Pro forma for individualized written plans for schools, day care centers, and camps will be provided to local teams.Insulin pump therapy initiation: Patients and families who wish to commence insulin pump therapy will be enrolled in an outpatient education program comprising a 1-hour group pre-pump education workshop with a diabetes educator and dietitian, followed by a 1-hour face-to-face session with the educator and pump company representative for commencement of the pump. Daily phone follow-up was provided for the week after pump initiation to adjust insulin doses until euglycemia was achieved. Insulin pump therapy is not commenced until at least 3–6 months after diagnosis to allow for maximal familiarization with MDI administration.Stabilization admissions: At the team’s discretion, elective admissions to the hospital are utilized to repeat the inpatient education program and adjust insulin doses.Hospital staff education: A hospital procedure document on insulin administration, hypoglycemia management, mealtime routine, and glycemic target is available in hard copy on pediatric wards and on the hospital intranet. Thirty-minute face-to-face training sessions with ward nursing staff are delivered by diabetes educators or dietitians at 3–4 monthly intervals, or as requested by ward staff. Dietitians oversee carbohydrate counting of hospital meals to allow for accurate insulin dosing in hospitals. A written dietary guide, individualized to the child’s age, was provided to the nursing staff to inform them of the appropriate carbohydrate quantities for each meal and snack.

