
### Implementation intervention

A multi-component clinical practice change intervention will be implemented at each site over an 18-month phase to support embedding SWIIM into the participating sites. Clinicians will be supported to provide the SWIIM program as part of the routine inpatient and outpatient management of T1D in children and adolescents. Through collaborative review with JHCH and implementation site clinicians, aspects of both inpatient and outpatient delivery of SWIIM may be adjusted to suit the local context and the available resources. Deviations from the standard SWIIM implementation will be reported in the final analysis.

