### Statistical analysis

The primary analysis will evaluate the change in glycemic control, measured by HbA1c at the individual level, from the 6-month pre-implementation baseline period to the end of the 18-month implementation period. Data will be modeled at the patient level, with clinic means over time used as the primary summary measure for interpretation.

A linear mixed-effects segmented regression model will be fitted, with fixed effects for time pre-intervention (monthly index), period (0 = per-implementation, 1 = implementation), time post intervention (which is zero during pre-intervention months and increments monthly thereafter), site, and patient-level covariates: age, sex, diabetes duration, Aboriginal and Torres Strait Islander status, and SEIFA quintile. The model will include a random intercept for patients to account for potential repeated measurements, and an autoregressive (AR(1)) correlation structure will be examined to account for within-patient autocorrelation over time. Effects will be expressed as (i) immediate level change and (ii) change in monthly slope, both relative to the counterfactual pre-implementation trends. Robust (sandwich) standard errors were calculated. Distributional and other modelling assumptions will be assessed by inspecting residual plots, with transformations or different distributional families (e.g., proportional odds logistic models) considered. Secondary outcomes with repeated measures will be assessed using a similar model with an appropriate distributional family dependent on the outcome type.

To assess the impact of medical outreach clinics in the MNCLHD prior to the study onset, an additional comparison of the primary outcome will be made from the commencement of medical outreach clinics to the commencement of the implementation period.

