## Discussion

There is a recognized need for improved access to evidence-based best practice care for children and adolescents with T1D in Australia and internationally. The disparity in outcomes reported between centers in Australia and globally indicates a knowledge gap regarding options for optimizing T1D education delivery and management strategies to achieve internationally recommended targets.

To our knowledge, this is the first prospective study that addresses this knowledge gap in both metropolitan and non-metropolitan settings. The pre-post study design is feasible for completion within non-metropolitan sites with limited resources. The study protocol was developed with researchers embedded within the clinical team and with the support of key stakeholders in local health districts, maximizing the chance that clinically relevant changes will be reliably detected and measured.

A limitation of this study is the lack of a contemporaneous control group for comparison. As the intervention is practice-wide, randomization of participants to a within-center control group is not possible. There is a lack of publicly available benchmarking data to provide a comparison group for individuals who do not attend the enrolled centers. Therefore, the causal attribution of the observed changes must be interpreted with caution.

The implementation strategies in this study were developed according to established implementation science frameworks and using feedback from clinicians involved in diabetes care. If positive changes in clinical and operational outcomes are demonstrated, this study will provide evidence to support the implementation of SWIIM in other services and health districts. This study may also provide a framework for implementing other management programs in non-metropolitan areas.

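### As worded, the hospitalization outcome would include SWIIM's own elective stabilization admissions, so its pre–post change can mix programme delivery with unplanned admissions

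*Protocol article*

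**What the plan says.** Under Secondary clinical outcome measures, the Protocol article lists "Number of hospitalizations for diabetes in the 12 months preceding implementation to study completion (not including initial diagnosis"). The abstract names the same outcome within "insulin therapy modality, adherence to complication screening, hospitalization rates, and program feasibility indicators". Neither place separates planned from unplanned stays. The data source is existing records: "Additional patient clinical outcome data were obtained from the electronic medical records at the MNCLHD and NBMLHD sites throughout the pre-intervention and implementation periods".

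Under SWIIM model of care, a list opens with "The model of care will be delivered to families with the following components". One item is stabilization admissions, left to the team's judgement, in which "elective admissions to the hospital are utilized to repeat the inpatient education program and adjust insulin doses". Under Implementation intervention, sites have latitude: "aspects of both inpatient and outpatient delivery of SWIIM may be adjusted to suit the local context and the available resources".

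For the analysis, the Statistical analysis section says: "Secondary outcomes with repeated measures will be assessed using a similar model with an appropriate distributional family dependent on the outcome type". The Discussion acknowledges: "A limitation of this study is the lack of a contemporaneous control group for comparison".

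**The concern.** An outcome used to judge a programme should not count the delivery of that programme as an event. Here the definition and the component list overlap. An elective stay to repeat diabetes education is a hospitalization for diabetes, and it is not the initial diagnosis. The definition removes the first inpatient education stay but not a later stay that repeats it.

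The pooled count then has two parts that can move in opposite directions. A fall in unplanned admissions would be a clinical gain. A rise in elective stays would show that the programme is being delivered. Their sum cannot be read as either. With no concurrent control group, any rise in elective stays that comes with SWIIM falls in the implementation period and enters the estimated level or slope change. Because stabilization is discretionary and inpatient delivery may be adapted locally, the mixture may also differ between sites.

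**Working it through.** The article states no hospitalization rate, expected effect or power for this outcome, so there is no figure to reproduce. The sample size calculation concerns HbA1c only. The check has two parts.

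**1. Does the definition include elective stabilization stays?**

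- Inclusion rule: hospitalization for diabetes. A stay to repeat diabetes education and adjust insulin meets it.
- Exclusion rule: initial diagnosis. A repeat stay does not meet it.
- Other filters: none in the abstract, the outcome list or the statistical analysis section.

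Read as written, such stays count.

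**2. How many added elective stays would matter?**

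Inputs, all assumed because the article gives none, per 100 patient-years:

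- u0, unplanned rate before implementation: 10, 15 or 20
- r, true relative fall in unplanned admissions: 20% or 30%
- e, elective stays added by SWIIM over usual care: 2, 5 or 10

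Taking no elective stays beforehand, the counted rate ratio is

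(u0 × (1 − r) + e) / u0 = 1 − r + e/u0.

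It equals 1 when e = u0 × r. Counting unplanned stays alone, the ratio is 1 − r.

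| u0 | r | Unplanned only | Counted, e = 2 | Counted, e = 5 | Counted, e = 10 | Break-even e |
|---|---|---|---|---|---|---|
| 10 | 20% | 0.80 | 1.00 | 1.30 | 1.80 | 2 |
| 10 | 30% | 0.70 | 0.90 | 1.20 | 1.70 | 3 |
| 15 | 20% | 0.80 | 0.93 | 1.13 | 1.47 | 3 |
| 15 | 30% | 0.70 | 0.83 | 1.03 | 1.37 | 4.5 |
| 20 | 20% | 0.80 | 0.90 | 1.05 | 1.30 | 4 |
| 20 | 30% | 0.70 | 0.80 | 0.95 | 1.20 | 6 |

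Worked line: u0 = 10, r = 30%, e = 5 gives (7 + 5)/10 = 1.20, where the unplanned ratio is 0.70.

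Over this grid the counted ratio runs from 0.80 to 1.80, and break-even from 2 to 6 added stays per 100 patient-years.

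**If usual care already used elective stays** at a rate e0, the ratio is (u0 × (1 − r) + e0 + e)/(u0 + e0). It still equals 1 when e = u0 × r, so break-even depends only on the increase e.

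**In numbers of stays.** The article gives 330 current patients, a minimum recruitment of 100 and an 18-month implementation period. Assuming full follow-up, 330 × 1.5 = 495 patient-years, so 2–6 per 100 is about 10–30 stays (9.9 to 29.7) across three sites. With 100 patients, 100 × 1.5 = 150 patient-years, or 3–9 stays.

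**The case against.** **The article does not say outright that stabilization stays are counted, and a fuller document may hold the coding rules.** The first half is right: inclusion is inferred from the wording. But this is more than an omitted detail. The article states an exclusion rule, and applying that rule leaves these stays in.

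**Elective stays may already be part of usual care.** This stands. A reader might infer that SWIIM introduces a new type of admission, but the account of the services covers staffing and clinic frequency and is silent on elective admissions. If their rate does not change, the counted ratio cannot cross 1 in the wrong direction, though it is diluted. For example, u0 = 10, r = 30%, e0 = 5 and e = 0 gives (7 + 5)/15 = 0.80 instead of 0.70.

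**The look-back is 12 months and implementation lasts 18, so a reader might infer that raw counts would inflate by 18/12 = 1.5.** The documents do not support this. The abstract speaks of rates, and repeated secondary outcomes get a model similar to the monthly segmented regression. Nothing announces a comparison of a 12-month total with an 18-month total.

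**A reader might infer that this is the only outcome able to show acute harm.** It is not: the same list collects time below range and level 2 hypoglycemia from CGM, and hospitalization is not labelled a safety endpoint.

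**Total diabetes admissions are a legitimate measure of service use.** Agreed, and elective stays consume real resources. That is a reason to keep all admissions in the cost-effectiveness analysis, not to let the pooled count serve as the clinical outcome.

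**The Discussion already urges caution on causal attribution.** That caution concerns the missing control group. It does not tell a reader which kind of admission changed.

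**Conclusion.** The point holds in conditional form. As worded, the outcome would include elective stabilization admissions that are themselves a component of SWIIM. If SWIIM increases these stays relative to usual care, the pre–post change mixes delivery with unplanned admissions and can mask or reverse a real change.

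The illustration rests wholly on assumed rates. Within them, 2–6 added elective stays per 100 patient-years cancel a true 20–30% fall; with fewer, some apparent benefit remains. The actual size and even the presence of bias are unknown, because neither the prior nor the expected frequency of elective stays is given. One secondary outcome is affected, and the primary HbA1c analysis is not.

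**What to change.** Change the measurement and reporting only; nothing in clinical care needs to change.

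- Classify each diabetes admission in both periods as elective stabilization or unplanned, with the recorded cause, using the same rule before and after implementation.
- Define the clinical outcome as unplanned diabetes admissions, excluding initial diagnosis, analysed as a rate in line with the abstract.
- Report elective stabilization stays separately, by site and period, as a measure of programme delivery.
- Keep all admissions in the cost-effectiveness analysis.

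The cost is one further field (type and cause) from records already being extracted. The downside is fewer events in the unplanned outcome, and so less precision.

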## Methods

### Study design and setting

A pre-post implementation study will be conducted at three sites providing outpatient and inpatient pediatric diabetes care in New South Wales (NSW), Australia. Two of the sites (Port Macquarie and Coffs Harbour) are level 5 public hospitals in the Mid-North Coast Local Health District (MNCLHD). The third center (Nepean) was a level 6 tertiary public hospital in the metropolitan Nepean Blue Mountains Local Health District (NBMLHD). The characteristics of the health districts in comparison to the JHCH, where SWIIM was developed, are presented in **Supplementary Table 2**. The sites were selected to allow analysis of SWIIM implementation in a variety of settings with differing staffing levels and diabetes-specific expertise across metropolitan and non-metropolitan populations.

The implementation of a practice change intervention will occur over an 18-month period (**Supplementary F****igure 1**), during which eligible patients will be recruited. The intervention will be delivered simultaneously across the three sites. Given that the intervention occurs at a site-wide level, a within-center randomization protocol would not be possible. Pre-intervention (usual care) data will be retrospectively obtained from the electronic medical records of recruited the patients. Patients who are newly diagnosed during the study period or for whom retrospective data are not available will also be included for statistical analysis at the available time points (see *Statistical analysis*).

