### Participants and recruitment

#### Pediatric diabetes services

In the MNCLHD, where there are 110 young people with type 1 diabetes, the average HbA1c level is 8.6%. Each of the two sites is served by a general pediatrician, diabetes educator, and dietitian. The diabetes educator and dietitian were also shared with adult diabetes services. The inpatient ward at each site is a mixed pediatric unit staffed by pediatric trained nurses, and there is access to social workers and Aboriginal health officers that service the entire hospital. Pediatric endocrinologists from JHCH provide six monthly outreach clinics to MNCLHD, an arrangement that began 24 months prior to the study commencement. Patients are reviewed in outpatient clinics three to four times per year.

In NBMLHD, where there are 220 young people with T1D, the average HbA1c level is 8.1%. The team comprises pediatric endocrinologists, dietitians, diabetes educators, and social workers. Patients are reviewed in outpatient clinics three to four times per year. The inpatient ward is a mixed pediatric unit staffed by pediatric trained nurses and there is access to Aboriginal health officers.

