#### Young people with type 1 diabetes

All young people aged 0–18 years with an existing diagnosis of type 1 diabetes or a new diagnosis within the study period in the catchment area of the three study sites will receive SWIIM education and management from local teams as part of routine care. Patients and their accompanying carers will be recruited by local clinicians for data collection as part of the study at their first face-to-face contact point during the intervention period. Written consent will be obtained to complete the satisfaction questionnaires and collect clinical data as part of the study. Patients and carers will have the opportunity to decline participation in the study or withdraw their consent at any point. Participation in the study did not alter the patient’s receipt of SWIIM as part of clinical care given the practice-wide intervention.

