### Power and sample size calculation

Based on the analysis of longitudinal JHCH clinical data, the within-patient variability for HbA1c is low (standard deviation of 0.6% over a 12-month period). To detect a change in HbA1c of 1% at a significance level of 0.05 with power 0.9, the sample size across the three sites needed is 25. If the within-patient variability at the three sites was double that of JHCH (standard deviation of 1.2%), the required sample size would be 90. Allowing for a loss-to-follow-up of 10%, we would aim to recruit a minimum of 100 patients at baseline. There are currently 330 patients across the three sites, and recruitment will continue throughout the study for newly diagnosed patients, with a potential sample size of approximately 400 at study close. This would allow for a recruitment rate of 33% to ensure that the sample size is met.

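### An admission can be the recruiting event and is then counted as a post-implementation hospitalization, so the pre-post admission contrast is open to bias if reach or consent depends on being admitted

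*Protocol article*

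**What the plan says.** Four statements in the protocol article bear on this outcome.

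- **Outcome** (Secondary clinical outcome measures): "Number of hospitalizations for diabetes in the 12 months preceding implementation to study completion (not including initial diagnosis"). The diagnosis admission is the only one left out.
- **Entry** (Young people with type 1 diabetes): patients and carers "will be recruited by local clinicians for data collection as part of the study at their first face-to-face contact point during the intervention period". No setting is named. Study design and setting describes "three sites providing outpatient and inpatient pediatric diabetes care", so a contact can be on a ward.
- **Source of pre-period data** (Study design and setting): "Pre-intervention (usual care) data will be retrospectively obtained from the electronic medical records of recruited the patients". Patients who are not recruited contribute to neither period.
- **Model** (Statistical analysis): secondary outcomes with repeated measures get a model like the primary one, with a patient random intercept and a suitable distributional family. Nothing is said about the recruiting event.

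Two further statements bear on how likely entry by admission is. Under Pediatric diabetes services, "Patients are reviewed in outpatient clinics three to four times per year" applies in both health districts. Under Power and sample size calculation, "This would allow for a recruitment rate of 33% to ensure that the sample size is met".

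**The concern.** Recruitment requires a contact in the post period, and that contact may itself be an outcome event. Nothing comparable is required in the pre period. Admissions could then enter the post count because they brought the patient into the study, while patients with no admission and no clinic visit drop out of both periods.

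There are two routes. A patient who does not come to clinic in the 18 months is seen only if admitted. Alternatively, a family may be more or less likely to consent on a ward than in clinic. A patient random intercept does not remove selection on a post-period event.

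At stake is the reading of the hospitalization result. A spurious rise could hide a real fall or suggest harm, and a spurious fall could flatter the program. There is no concurrent control group to reveal either. If admissions are costed in the cost-effectiveness analysis, the error would carry over; the protocol does not list the cost inputs.

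**Working it through.** The protocol gives no hospitalization figure, so there is none to reproduce. The check asks what post/pre rate ratio the stated rules give when nothing truly changes.

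**Inputs from the protocol.** Pre window 12 months; post window 18 months (1.5 years); three to four clinic reviews a year, taken as 3.5; 33% recruitment treated as sufficient.

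**Assumed inputs.** Admission rate λ of 0.05 to 0.15 per patient-year; first clinic visit uniform over 12/3.5 = 3.43 months, so a mean wait of 1.71 months; share p of patients with no clinic visit in 18 months; their admission rate r times that of attenders; consent of 33% to 100% by setting.

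**1. Everyone attends, equal consent.** The probability of entering by admission is about λ × 1.71/12: 0.7% at λ = 0.05 and 2.1% at λ = 0.15. These patients are recruited with the same probability as everyone else, and the count runs from the start of implementation for all. The recruited group is therefore not selected on admissions and the ratio is 1.00. Simulation gave 0.99 to 1.02 at both 100% and 33% recruitment.

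**2. Everyone attends, ward consent k times clinic consent.** Admissions before the first clinic visit make up 1.71/18 = 0.095 of post-period admissions and are weighted by k. To first order:

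ratio ≈ 1 + (k − 1) × 0.095

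| Clinic / ward consent | k | Formula | Simulated |
|---|---|---|---|
| 33% / 50% | 1.52 | 1.05 | 1.03–1.06 |
| 33% / 66% | 2 | 1.10 | 1.07–1.10 |
| 33% / 100% | 3.03 | 1.19 | 1.12–1.22 |
| 50% / 25% | 0.5 | 0.95 | 0.95–0.96 |

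The simulations in this table ran λ up to 0.4.

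**3. Some patients reached only by admission, equal consent.** A non-attender enters with probability 1 − exp(−1.5rλ). All of this group's post-period admissions are captured, but only that fraction of its pre-period admissions:

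ratio = [(1 − p) + pr] / [(1 − p) + pr(1 − exp(−1.5rλ))]

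- p = 0.10, r = 3, λ = 0.05: 1.20 / (0.90 + 0.30 × 0.2015) = 1.25.
- p = 0.05, r = 3, λ = 0.15: 1.10 / (0.95 + 0.15 × 0.4908) = 1.07.

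Simulation over p = 0.05 to 0.10 with r = 3 gave 1.04 to 1.25; the lower values come from rates that vary between patients. With r = 1 and p = 0.05 to 0.20 it gave about 1.02 to 1.23.

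**4. Both routes.** For p = 0.10, r = 3, λ = 0.05 and k = 2:

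- numerator: 0.90 × 1.095 + 0.30 × 2 = 1.586
- denominator: 0.90 × 1.007 + 0.30 × 2 × 0.2015 = 1.027
- ratio: 1.54

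Simulations with p = 0.05 to 0.10 and r = 3 ran from 1.13 to about 1.5, with single runs at the extreme corner up to 1.60. With p = 0.10 and r = 1 they gave 1.11 to 1.29.

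**5. Candidate remedies, same settings.**

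- Dropping the recruiting admission but keeping the full 18 months gives 0.81 to 0.92, an undercount.
- Also starting person-time at recruitment gives a crude ratio of 0.92 to 1.04. The low values arise because high-rate patients recruited late on the ward keep 12 full pre-period months but have little post time.
- A within-patient comparison with a person-time offset removes that imbalance: 0.98 to 1.02 in every setting, including lower ward consent.

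**The case against.** A reader might infer that reported admissions will rise under SWIIM simply because the recruiting admission is counted. The documents do not support that. The window opens at implementation for every recruited patient, not at entry, and step 1 gives a ratio of 1.00.

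The bias needs a fact the protocol does not state: patients never seen in clinic over 18 months, or consent that differs by setting. The text leans towards clinic recruitment. Three to four reviews a year imply about four to six scheduled contacts in 18 months, and the questionnaires start at the initial outpatient visit. The 33% figure is the rate sufficient for the HbA1c sample size; it is not a plan for partial recruitment and says nothing about consent by setting. Families of acutely ill children may be harder to consent, which reverses the sign.

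Precision also limits the importance. At an assumed 0.1 admissions per patient-year, 100 patients give about 10 pre and 15 post events, so the standard error of the log ratio is √(1/10 + 1/15) = 0.41. With 330 patients (33 and 50 events) it is about 0.22. A ratio of 1.25 has a log of 0.22, no larger than that noise. Event-counting detail may also sit in a fuller document, and the article already urges caution about causal attribution.

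Most of this stands: it makes the point conditional and keeps its weight down. It does not remove the point, because the entry rule and the outcome definition are both stated here and together let an outcome event select patients. Scheduled reviews do not guarantee attendance, and the protocol itself measures adherence to follow-up as a feasibility outcome.

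**Conclusion.** The point holds as a conditional risk to one secondary outcome. The stated rules allow an existing patient to enter through an admission that is then counted after implementation, with no matching condition before it. This is harmless if everyone is reachable in clinic and consent does not depend on setting. Otherwise the contrast is biased, more probably upward than downward. With no true change the ratio runs from about 0.95 (ward consent half of clinic consent) to about 1.5 (10% non-attenders at three times the admission rate, ward consent doubled).

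Those limits depend on assumed admission rates, attendance and consent, and describe a crude rate ratio, not the planned segmented mixed model. The protocol fixes neither the size nor the direction. The primary HbA1c analysis is outside this check. Importance is low to moderate; the change is worth making mainly because it is cheap and protects in both directions.

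**What to change.** In Secondary clinical outcome measures, state that for existing patients the post-implementation hospitalization count and person-time start just after the recruitment contact, so that a recruiting admission is not counted. Both parts are needed, since dropping the admission alone undercounts.

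Analyse admissions as a rate with a person-time offset, compared within patient against the 12 pre-implementation months. The planned patient-level effect serves this purpose; a conditional Poisson model would be the strict form.

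Record the recruitment setting (clinic or ward). As sensitivity analyses, report the count from the start of implementation, and the ward-recruited patients separately.

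The cost is a short addition to the outcome definition and one field at recruitment. The mean wait of 1.71 months takes about 10% of post-period person-time (1.71/18 = 9.5%), leaving about 1.35 instead of 1.5 years per patient. It needs no extra patients or procedures.
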